### 2.4 Sample size estimation

Sample size estimation was conducted utilizing the G*Power software package (version 3.1.9.7) based on the methodology outlined in the study by Fonta et al. (2021). The input parameters included the following: the statistical test was repeated measures, within factors; the α error probability was 0.05; the effect size F was 0.25; power (1 − β error probability) was 0.80; correlation among repeated measures was 0.70; and no sphericity correction (e = 1) was applied. It is important to note that the magnitude of the correlations (r = 0.7) can be considered large according to Hopkins et al. (2009). This correlation was chosen to reflect the anticipated relationship between the repeated measures in this study, based on the literature (Hopkins et al., 2009; Fonta et al., 2021; Zahiri et al., 2022). Consequently, the total sample size was determined to consist of seven subjects (in each trial). To ensure ample statistical power, especially in scenarios with smaller-than-expected effects or lower correlations between repeated measures, we decided to include 20 participants, who will be tested in the three experimental conditions. This approach also takes into account the possibility of participant dropouts during the study.

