### 2.7 Statistical analysis

The statistical analysis will employ SPSS Statistics software (Version 24; IBM Corporation^©^, United States). To evaluate the normality of core and postural stability, as well as EMG variables, a Shapiro-Wilk test will precede any comparative analyses. For normally distributed data, a two-way ANOVA will be applied to explore the main effects of recovery modalities and time intervals, along with any potential interactions between these factors. The factors under consideration include the type of conditions [trunk stabilization exercises session, foam rolling exercise session, passive recovery] and testing time [T1: baseline, T2: immediately after modified Abt’s fatigue protocol, T3: immediately after recovery modalities, and T4: 15 min after recovery modalities]. To identify significant differences, Bonferroni *post hoc* comparisons will be conducted as necessary.

For non-normally distributed data, nonparametric tests will be utilized. Friedman’s test, followed by Dunn’s *post hoc* test, will be employed to compare core and postural stability, as well as EMG variables across testing times [T1, T2, T3, and T4]. The Kruskal-Walli’s test will be utilized for between-condition mentioned above comparisons at each testing time.

Data will be presented as mean ± standard deviation (SD). Effect sizes for both between-session and within-session comparisons of all quantitative variables will be evaluated using Cohen’s d coefficient: small effect (d < 0.2 and ηp2 = 0.01); moderate effect (d ≈ 0.5 and ηp2 = 0.06); and large effect (d > 0.8 and ηp2 = 0.14) (Cohen, 2013). The significance level (α) will be established at 0.05 for all statistical tests.

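### Optional improvement: Holm's step-down in place of Bonferroni for the modality contrasts would give a few points more power at the same family-wise error rate

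*Protocol article*

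**What the plan says.** For normally distributed variables, section 2.7 plans a two-way ANOVA with condition (three modalities) and testing time (T1 to T4) as factors, looking at both main effects and their interaction. The follow-up method is Bonferroni, and on when it applies the section says only that "comparisons will be conducted as necessary". The sentence covers time comparisons as well as modality comparisons, and it does not define the family over which the correction runs. On the error level the section says: "The significance level (α) will be established at 0.05 for all statistical tests".

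Section 2.4 sizes the trial on a repeated-measures, within-factors F test with alpha 0.05, a target power of 80% and epsilon set to 1. The assumed effect is given as "the effect size F was 0.25". For the dependence between a person's measurements, the section states that the "correlation among repeated measures was 0.70". That calculation gives seven participants, and the trial takes 20. The article makes no statement about the power of any pairwise comparison.

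**The concern.** Three modalities give three pairwise contrasts. Bonferroni tests each at 0.05/3 = 0.0167. Holm orders the p-values and tests the smallest at 0.0167, the next at 0.025 and the last at 0.05, stopping at the first failure. Its family-wise guarantee is the same under any dependence between the tests, and it can only add rejections.

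The difference matters most where more than one rejection is needed. The article expects both exercises to improve core and postural stability and includes passive recovery as the third condition. If improvement is judged against passive recovery, the claim for both exercises needs two rejections. With 20 people and single-step thresholds, some power for that joint finding is given up.

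**Working it through.** **Inputs from the article.** N = 20, each person in all three conditions (2.4, 2.5.2); correlation 0.70, f = 0.25, epsilon = 1 (2.4); alpha 0.05 (2.4, 2.7).

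**Assumptions.** One family of three modality contrasts at a single time point; two-sided paired t tests; no dropout; the contrasts are tested without conditioning on a significant ANOVA; trunk stabilization and foam rolling have equal means, and both differ from passive recovery by d.

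**1. The article's own power basis.** For the omnibus F test with m measurements per person:

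λ = f² · N · m / (1 − r), df1 = m − 1, df2 = (N − 1)(m − 1)

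The article does not state m. At N = 20:

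| m | λ | df | Power |
|---|---|---|---|
| 3 | 0.0625 × 20 × 3 / 0.30 = 12.5 | 2, 38 | 0.87 |
| 4 | 0.0625 × 20 × 4 / 0.30 = 16.7 | 3, 57 | 0.93 |
| 12 | 0.0625 × 20 × 12 / 0.30 = 50 | 11, 209 | above 0.99 |

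The post hoc method does not enter any of these. The smallest N reaching power 0.80 is 17, 15 and 8 for m = 3, 4 and 12. The stated seven is therefore not reproduced exactly, and with m unstated this cannot be settled. It is a separate matter and has no bearing on this point.

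**2. What f = 0.25 means for a contrast.** For means (d, d, 0) the SD of the means is d√2/3. Setting this to 0.25 gives d = 0.25 × 3/√2 = 0.53 SD. A working value of 0.5 SD is slightly below that.

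**3. Bonferroni power in closed form.** The SD of a paired difference is √(2 × 0.30) = 0.775. At d = 0.5 the noncentrality is 0.5 × √20 / 0.775 = 2.89. The critical value of t on 19 df at two-sided 0.0167 is 2.63. Power per active-versus-passive contrast is 0.61.

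**4. Bonferroni against Holm by simulation** (40,000 trials per row, both methods applied to the same p-values):

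| d (SD) | Per active-vs-passive contrast | Both active-vs-passive contrasts | At least one rejection |
|---|---|---|---|
| 0.4 | 0.40 → 0.43 | 0.23 → 0.29 | 0.57 → 0.57 |
| 0.5 | 0.61 → 0.65 | 0.44 → 0.52 | 0.77 → 0.77 |
| 0.53 | 0.67 → 0.71 | 0.51 → 0.59 | 0.82 → 0.82 |
| 0.6 | 0.79 → 0.82 | 0.67 → 0.74 | 0.91 → 0.91 |

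Repeat runs differ by up to about 0.01.

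**5. Error rate.** With no difference between any modalities, the chance of any rejection was the same for both methods, between 0.045 and 0.048 across runs. With the two active modalities truly equal and d = 0.5, the false rejection rate for trunk stabilization versus foam rolling rises from about 0.017 to 0.032, still below 0.05.

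**6. Another pattern.** With evenly spaced means at f = 0.25 (steps of 0.31 SD), the largest contrast goes from 0.809 to 0.817 and each smaller one from about 0.22 to 0.30. The chance of at least one rejection is 0.832 for both methods.

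**7. Fewer completers.** With 17 completers (assumed) and d = 0.5, power to show both contrasts goes from 0.34 to 0.41.

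**The case against.** The strongest reply is that nothing here is wrong. Bonferroni is valid, standard and prespecified, and the article never calls it the most powerful choice. That stands, and it is why the point is only an improvement.

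A reader might go further and infer that the trial gives up power for no return. The documents do not support that. Bonferroni brings simple simultaneous intervals that match its tests, and these suit the abstract's hypothesis that the two active modalities are equally effective; more power to reject equality does not help to show equivalence. The omnibus power on which the trial was sized and the chance of at least one pairwise finding are both untouched. Nor is the Bonferroni sentence restricted to modality contrasts; the three-contrast family is an assumption of this check.

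Two further objections carry less weight:

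- With three pairwise contrasts, Shaffer's step-down is stronger still (0.62 for both contrasts at 0.5 SD). That does not make Holm any less of a gain over Bonferroni.
- The stated purpose is trunk stabilization versus foam rolling, and there Holm roughly doubles the false rejection rate when the two are equal. It does so within the family-wise limit. The article's hypothesis that both exercises work still makes the contrasts with passive recovery relevant.

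**Conclusion.** The point holds as a cheap, optional improvement. At 0.5 SD, Holm adds about 4 points of power per active-versus-passive contrast and about 8 points for showing both, with the family-wise error rate still controlled at 0.05. Over 0.4 to 0.6 SD, the gain for showing both is about 6 to 8 points. It adds nothing to the chance of at least one finding, to the omnibus test or to a demonstration of equivalence.

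The sizes rest on the assumptions listed in the check. They apply only to the parametric branch and not to the Friedman and Kruskal-Wallis route. That Holm rejects everything Bonferroni rejects does not depend on those assumptions and holds for any family size.

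**What to change.** In section 2.7, name the three modality contrasts at T3 and the three at T4 as the families, and use Holm-adjusted p-values within each. Report Bonferroni simultaneous intervals for the same contrasts, above all for trunk stabilization versus foam rolling.

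No participants or measurements are added. The cost is a short ordering step outside the standard output, repeated at both times for every normally distributed variable. Holm also has no simple matching intervals, so a contrast may occasionally be significant by Holm while its Bonferroni interval includes zero. The plan should say beforehand that the Holm p-value decides the test and that the interval describes the size of the difference.

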
As explained earlier, the mechanisms for the effects of trunk stabilization exercises and foam rolling exercises on core and postural stability are described differently. It is hypothesized that both exercises will induce a significant improvement in core and postural stability. If foam rolling is found to be an effective exercise for recovery of impaired core and postural stability, core-specific exercises may not be necessary in the workplace. This would lead to a reduction in training time (Zahiri et al., 2022), which is a positive aspect of workplace exercise. This study presents a protocol for the investigating the modeling of the process of muscle fatigue and recovery to provide an opportunity to identify suitable workplace exercises. The purpose of this study will be to compare the immediate effect of trunk stabilization exercises on recovery of impaired core and postural stability induced by fatigue with that of foam rolling exercises in sedentary adults.

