#### 2.5.2 Experimentation

The experiment involves 20 participants, each completing three sessions spaced 1 week apart. In each session, they will perform a modified Abt’s fatigue protocol, consisting of eight exercises targeting their core muscles. Subsequently, they undergo recovery modalities. Everything will remain the same throughout the sessions except the type of recovery modality, which will be varied (trunk stabilization exercises, foam rolling exercises, and passive recovery). The order of the recovery modalities will be counterbalanced to control for potential sequence effects. Data will be gathered from participants at three different time points:1. Pre-fatigue assessment (baseline measurement).2. Post-fatigue assessment (immediately following the fatigue protocol).3. Post-recovery modalities assessment (immediately and 15 min after the completion of active and passive modalities, respectively).

Participants will be tested by the same examiners at the same time.

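### In the non-normal branch, Dunn's test after a four-time Friedman ranking lets T1 and T4 influence the T2–T3 verdict and loses power when recovery is gradual and incomplete

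*Protocol article*

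**What the plan says.** Section 2.7 first applies a Shapiro-Wilk test. Normally distributed outcomes go to a two-way ANOVA with Bonferroni comparisons. For the rest, "For non-normally distributed data, nonparametric tests will be utilized", and the procedure over time is named: "Friedman’s test, followed by Dunn’s *post hoc* test, will be employed to compare core and postural stability, as well as EMG variables across testing times". The times are T1 (baseline), T2 (directly after the fatigue protocol) and then "T3: immediately after recovery modalities, and T4: 15 min after recovery modalities". A separate Kruskal-Wallis test compares the modalities at each time. On the error level: "The significance level (α) will be established at 0.05 for all statistical tests".

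The section names Bonferroni only for the ANOVA branch. For the Friedman branch it gives neither a multiplicity adjustment nor a restricted set of pairs.

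Section 2.5.2 fixes the size: "The experiment involves 20 participants, each completing three sessions spaced 1 week apart". The Introduction gives the purpose, to "compare the immediate effect of trunk stabilization exercises on recovery of impaired core and postural stability induced by fatigue" with that of foam rolling. The main question is therefore a comparison of modalities. The T2-to-T3 change within one modality is a supporting result.

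**The concern.** The within-modality question is whether a person's value directly after recovery (T3) differs from that person's value directly after fatigue (T2). Dunn's test after Friedman does not use those pairs on their own. It ranks each person's four values together, averages the ranks by time and compares the averages. Its standard error is derived for the case where all four times are exchangeable, with neither fatigue nor recovery. This design sets out to break that condition, because fatigue is induced before T2.

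Two consequences follow. First, T1 and T4 influence a verdict that is meant to concern T2 and T3 only. Second, if nearly everyone's T2 and T3 values are neighbours in the ranking, the mean-rank gap stays near 1 however large the improvement. Under gradual, incomplete recovery the same holds for T4 versus T1, so a deficit left in nearly everyone at 15 minutes could be reported as non-significant and be mistaken for full recovery.

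**Working it through.** **Inputs.** n = 20 (section 2.5.2); k = 4 times, hence 4×3/2 = 6 pairs (section 2.7); α = 0.05 (section 2.7), taken as two-sided. The protocol gives no figure of its own for this branch. Assumptions: the rank order T1 best, T4, T3, T2 worst, and Bonferroni over six pairs. The simulations take r = 0.70 from section 2.4.

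**Adjacent-rank limit.**
- Standard error of a mean-rank difference: √[k(k+1)/(6n)] = √[20/120] = 0.408.
- If all 20 people have the assumed order, the T2–T3 gap is 4 − 3 = 1.
- z = 1/0.408 = 2.449; two-sided p = 0.0143; ×6 = 0.086.
- Smallest gap that is significant at 0.05/6: 2.638 × 0.408 = 1.077, which is above 1.
- Smallest n at which a gap of 1 is significant: 2.638² × 20/6 = 23.2, so 24 (adjusted p = 0.044).
- With 19, 18 or 17 completers the adjusted p is 0.102, 0.121 or 0.144.

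Friedman's chi-square is then at its maximum: (12×20)/(4×5) × [(−1.5)² + 1.5² + 0.5² + (−0.5)²] = 12 × 5 = 60. A paired sign test or exact Wilcoxon test with 20 of 20 improving gives 2 × 0.5²⁰ = 1.9×10⁻⁶. The large-sample Wilcoxon p is 8.9×10⁻⁵.

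**How fragile the limit is (n = 20).**

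| Change | p for T2–T3 |
|---|---|
| 1 person with a two-rank gap (mean gap 1.05, z = 2.572), ×6 | 0.061 |
| 2 people with a two-rank gap (mean gap 1.10, z = 2.694), ×6 | 0.042 |
| T3 and T4 equally often the better (mean gap 1.5), ×6 | 0.0014 |
| Gap of 1, Holm or three preselected pairs | 0.043 |
| Gap of 1, unadjusted | 0.014 |

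The Holm or three-pair figure rises to 0.051 with 19 completers.

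**Power for T2 versus T3.** Simulated with n = 20, r = 0.70, log-normal data, both tests ×6 and 1,500 replicates. Means are in SD units on the log scale. Repeat runs differ by a few points.

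| Means T1, T2, T3, T4 | Dunn | Wilcoxon |
|---|---|---|
| *Gradual, large* | | |
| 0, 2.4, 1.6, 0.8 | 14% | 86% |
| 0, 3, 2, 1 | 12% | 97% |
| 0, 2, 1.2, 0.5 | 23% | 85% |
| *Near-complete at T3* | | |
| 0, 0.8, 0, 0 | 85% | 86% |
| 0, 0.8, 0, 0.4 | 87% | 85% |
| 0, 1, 0.2, 0.2 | 81% | 86% |
| 0, 0.65, 0, 0 | 65% | 67% |

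Moderate gradual patterns fall between, for example 35% against 60% and 44% against 57%.

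**Dependence on T4.** With T2 and T3 held at 1.6 and 0.8 SD, moving only T4 from 0.8 to 0 drops Dunn from 66% to 32%. Wilcoxon stays at 86%.

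**Residual deficit, T4 versus T1** (0, 3, 2, 1): Dunn 13%, Wilcoxon 97%.

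**Complete null.** Dunn rejects T2–T3 in 0.9% of runs and Wilcoxon in 0.7%, so the replacement does not inflate error.

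**The case against.** Friedman followed by Dunn is a recognised procedure that controls error. The case for leaving it alone has real force on several points.

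- **The recovery pattern is not in the protocol.** Nothing says that T4 will be better than T3, or that both stay worse than T1. The stress on an immediate effect fits a T3 near baseline equally well, and there Dunn loses almost nothing. This stands. Gradual recovery is plausible after fatigue driven to a Borg score of 17 (section 2.5.4), but it remains an assumption.
- **The large-effect scenarios are far from the planned effect.** The three large patterns correspond to f of about 0.75 to 1.1, against the planned 0.25 in section 2.4. This stands, and the moderate patterns show a smaller loss.
- **The adjustment is unstated and may be left to an analysis plan.** This stands for the 0.086 limit. A change of adjustment alone does not cure the power loss, though: in the three large patterns Dunn with Holm reaches only 34%, 47% and 46%. Unadjusted it reaches 57%, 69% and 68%, with six tests per outcome uncontrolled.
- **Readers would still see a signal.** Friedman would be highly significant, and section 2.7 also requires within-session effect sizes. This softens the harm but does not correct the pairwise verdict.

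A reader might infer that this branch can never detect immediate recovery, or that the trial cannot answer its main question. The protocol supports neither. Two people with a two-rank gap are enough for significance. The main question compares modalities, and a within-modality p-value does not answer it.

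**Conclusion.** The concern holds in a limited form. The dependence of the T2–T3 verdict on T1 and T4 is a property of the named method and needs no assumption about the data. How much it costs depends on the recovery pattern: heavy under large partial recovery (about 12–23% power against 86–98%), noticeable under moderate partial recovery (about 35–44% against 57–60%), and negligible when recovery is near complete at T3. The floor of 0.086 on the adjusted p requires both the strict rank order in essentially everyone and Bonferroni over six pairs, so it illustrates the defect and does not predict the result. Only within-modality time comparisons for variables that fail the Shapiro-Wilk test are affected. Priority is minor to moderate: the paired test was about as powerful or clearly more powerful in the patterns examined, and the change is cheap.

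**What to change.** In section 2.7, keep Friedman's test as the omnibus test over the four times and replace the Dunn step with wording such as:

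> Within each recovery modality, paired Wilcoxon signed-rank tests will compare T1–T2, T2–T3, T2–T4, T1–T3 and T1–T4, with Holm adjustment over these five comparisons for each variable.

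Bonferroni over the five pairs would also do; what matters is that one adjustment is named. With 20 of 20 improving, the exact T2–T3 p after ×5 is 5 × 1.9×10⁻⁶ = 9.5×10⁻⁶ (5 × 8.9×10⁻⁵ = 4.4×10⁻⁴ with the large-sample p). T1–T3 belongs in the list because it tests for a deficit remaining directly after recovery.

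Do not add a switch to the sign test that depends on how the differences look. It would be another data-driven choice, and the sign test has less power (65%, 87% and 65% in the three large patterns).

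The cost is one sentence, with no extra data or participants. The small downside is that the signed-rank test assumes roughly symmetric paired differences.

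### The non-parametric branch compares the three recovery conditions with Kruskal-Wallis, an independent-groups test, although the same 20 people provide all three, and it compares only levels, not recovery

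*Protocol article*

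**What the plan says.** Section 2.5.2 sets out a within-person design: "The experiment involves 20 participants, each completing three sessions spaced 1 week apart". Only the recovery modality differs between sessions, and "The order of the recovery modalities will be counterbalanced to control for potential sequence effects". Section 2.4 agrees: "we decided to include 20 participants, who will be tested in the three experimental conditions". There the sample size rests on a matched analysis ("the statistical test was repeated measures, within factors"), and "correlation among repeated measures was 0.70".

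Section 2.7 then splits the analysis by a Shapiro-Wilk test. For normally distributed variables, "a two-way ANOVA will be applied to explore the main effects of recovery modalities and time intervals", together with their interaction. For the others, Friedman's test with Dunn's post hoc test is used across T1 to T4, and the Kruskal-Wallis "test will be utilized for between-condition mentioned above comparisons at each testing time". No interaction or change score is named in this second branch.

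**The concern.** Time and condition are both within-person factors. The non-parametric branch gives time a matched test and condition an unmatched one. Kruskal-Wallis judges the differences between conditions against all the variation in the pooled sample, including stable differences between people, which the design removes. With positive correlation between a person's sessions, the statistic is too small, the test rejects too rarely, and real differences between modalities are missed.

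The question also changes. The aim is to compare modalities on recovery from induced fatigue. The parametric branch does this through the condition-by-time interaction. The non-parametric branch compares levels at T1, T2, T3 and T4 separately and makes no use of each session's own post-fatigue value. The affected variables are the EMG and the core and postural stability measures, which are the primary outcomes.

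**Working it through.** **Inputs.** From section 2.4: 20 participants, f = 0.25, correlation r = 0.70, alpha 0.05. From section 2.5.2: three conditions per person. Assumed: normal data with a shared participant effect and equal correlations. Both tests use ranks only, so a lognormal version shifted on the log scale gives the same results, and skewness itself plays no part.

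**The plan's own figure.** Section 2.4 reports seven subjects. The usual formula has noncentrality λ = f²·N·m/(1 − r), with df m − 1 and (N − 1)(m − 1). The number of measurements m is not stated.
- m = 3 needs N = 17, and m = 4 needs N = 15.
- m = 12 (3 conditions × 4 times) needs N = 8, with λ = 0.0625 × 8 × 12/0.30 = 20.0. Power at N = 7 is 0.748.
- A three-group by four-time interaction needs 21 in total, or 7 per group (power 0.859).

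Seven is therefore reached or approached only with inputs that the article does not give. That does not affect this point. Every version divides by 1 − r, so the planning takes credit for the within-person correlation that Kruskal-Wallis leaves unused.

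**Why the test is conservative.** The difference between two condition means has variance 2σ²(1 − r)/n. An independent-groups test assumes 2σ²/n. At r = 0.70 and n = 20, in units of σ², these are 2 × 0.30/20 = 0.030 and 2/20 = 0.100, so the assumed variance is 3.3 times too large. At r = 0.5 the factor is 2, and at r = 0.3 it is 1/0.7 = 1.4. Rank tests behave in much the same way.

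**Simulation.** One testing time, n = 20, one condition shifted by 0.5 SD. The means 0, 0, 0.5 have SD √(1/18) = 0.24, close to the planned f of 0.25.

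| r | Kruskal-Wallis power | Friedman power | Kruskal-Wallis type I error |
|---|---|---|---|
| 0.3 | 26% | 35% | about 1.6% |
| 0.5 | 22% | 46% | about 0.4% |
| 0.7 | 17% | 70% | about 0.1% |

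Friedman's type I error stays at about 5%. Repeat runs differ by one or two percentage points in power. With equally spaced conditions at f = 0.25 and r = 0.7, the figures are 21% against 74%.

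**Larger effects.** With a 0.8 SD shift, power is 71% against 74% at r = 0.3 and 74% against 98% at r = 0.7. With f = 0.40 and r = 0.7 it is 82% against 99%. At r = 0, Kruskal-Wallis is no worse than Friedman.

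**Change from T2.** Under equal correlations, a T3 − T2 change has variance 2(1 − r)σ² = 0.60σ² at r = 0.7. The within-person residual of a level is (1 − r)σ² = 0.30σ². The variance doubles, and Friedman on changes has about 40% power for the 0.5 SD shift, not 70%.

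**The case against.** The strongest defence is that the error is conservative and confined to a contingent branch. It creates no excess false positives, and the article gives no distributions, so how many variables will reach this branch is unknown. Section 2.4 gives 0.70 for repeated measures in general and does not say that it applies between sessions a week apart, which is the correlation that matters here. All of this stands, which is why a range of r is shown. None of it makes an independent-groups test right for these data.

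Four stronger readings are tempting, and the documents do not support them.
- A reader might infer that the plan has no test of differential recovery. The parametric branch has one, through the interaction. Even in the other branch, comparing levels at T3 and T4 after the same fatigue protocol is an indirect modality comparison.
- A reader might infer that the parametric branch ignores the pairing too, since it says only two-way ANOVA. Section 2.4 names repeated measures, within factors, so a repeated-measures ANOVA is the natural reading. Adding the word is a clarification.
- A reader might infer that the pre-test will send many variables to the faulty branch by chance. Testing 12 independent normal cells at 5% gives at least one rejection with probability 1 − 0.95¹² = 46%. Section 2.7 states neither per-cell testing nor a one-rejection rule, so this figure rests on an assumption and carries no weight here.
- A reader might infer that a non-significant result will be taken as proof of the equal effectiveness hypothesised in the abstract. Section 2.7 does not say so. Low power would make such a misreading easier, but that is a separate matter.

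**Conclusion.** The point holds for the non-parametric branch. Kruskal-Wallis across conditions is a wrong stated rule, contradicted by sections 2.4 and 2.5.2, and not a detail left to a fuller document. At the protocol's planning correlation and an effect close to its planned f, it cuts power for a modality comparison at one testing time from about 70% to about 17%. The loss is moderate at r = 0.3 (35% to 26%) and smaller for large effects. These figures assume 20 complete participants and equal correlations, and they apply only to variables that fail the normality check. The same branch lacks any comparison of change or interaction, so it tests differential recovery only indirectly.

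**What to change.** In section 2.7, replace Kruskal-Wallis with Friedman's test across the three conditions at each testing time, followed by paired Wilcoxon signed-rank comparisons with the Bonferroni adjustment that the section already uses. Add the same paired comparison for change from T2 at T3 and at T4, so that this branch addresses recovery. As a clarification only, write two-way repeated-measures ANOVA in the parametric branch.

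The cost is wording: nothing changes in data collection or in the number of participants. There are two downsides. Change scores are noisier than levels (about 40% power at r = 0.7 under equal correlations), so the full gain to 70% applies to levels and not to change. Friedman's test also uses only participants with all three sessions. A single repeated-measures or mixed model with a participant effect and condition by time, fitted to suitably transformed data, is an acceptable alternative; its mixed form can also use incomplete participants.
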